## Sample size calculation

The sample size calculation of the present study was informed by data from a previous study [21] on psychological effects of high-intensity exercise, which showed a significant reduction in anxiety levels in 33 participants with anxiety disorders. We conducted a power calculation using https://clincalc.com/stats/samplesize.aspx. We assumed a baseline mean of 30 on the Beck Anxiety Inventory (BAI) for each group. The expected post-treatment BAI scores are 14 for the high-intensity group and 22 for the low-intensity group. With a significance level (alpha) of 0.05, SD of 7 and 80% power, the required sample size is 24. This means we need 12 participants per group to detect significant differences using a two-tailed *t*-test. Previous studies have found that the average attrition rate is 20% [33].

To account for an expected attrition rate of about 20% [33], the final target sample size is 30 participants (15 per group), representing the minimum required for adequate power. Additional participants may be included if recruitment permits, to further strengthen statistical power. Potential missing data will be addressed using linear mixed-model analyses, since this analysis is robust to missing-at-random mechanisms. Sensitivity analyses based on both intention-to-treat and per-protocol datasets will be applied to assess the robustness of the findings.

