### Participant adherence to the intervention, adverse events and concomitant care

The exercise physiologist will make appointments with the participants to perform the training interventions, and he will support adherence by following up on the participants, monitoring any adverse effects and providing real-time feedback.

Serious adverse events will be reported to the North Norway Regional Ethics Committee in accordance with the Health Research Act. Physical exercise is generally considered safe [34]; hence, no adverse events are expected; however, possible harms (e.g. injuries or severe events) are monitored using baseline values to oversee the condition of all participants during the trial.

Although the intervention is considered low risk, all participants will be continuously monitored for potential adverse events during each training session. The exercise physiologist and study nurse will record and report any untoward medical occurrences (e.g. cardiovascular symptoms, injuries, or other health-related complications).

In the event of any serious somatic or medical incident, the participant will immediately be withdrawn from the study and receive appropriate medical evaluation and treatment. The trial will be temporarily suspended or stopped if such events indicate that continued participation poses a health risk to any participant.

Serious adverse events will be reported to the Regional Committee for Medical and Health Research Ethics (REK North) and the Data Protection Officer in accordance with the Norwegian Health Research Act.

Given the short duration and low-risk nature of the intervention, no formal interim analyses or statistical stopping rules have been defined. The intervention is considered a low-risk and natural physical activity, similar to standard exercise routines recommended for the general population. Therefore, the likelihood of any serious adverse medical event is regarded as minimal.

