### Statistical analysis

Data management and analyses are performed using SPSS 30 (SPSS Inc., Chicago, IL, USA). Data will be analysed using descriptive and inferential statistics. Continuous variables are presented with mean ± SD and 95% CIs.

The effect of the intervention will be assessed by examining change scores on the BAI and HADS (primary outcomes) and blood pressure and EKG (secondary outcomes). Changes from baseline to post-tests (immediately, after four weeks, and after three months) will be analysed.

Single measures (e.g. baseline data) will be analysed using ANOVA or linear regression, provided the statistical assumptions for linear models are met. Variables will be assessed for normality through visual inspection of histograms and Q-Q plots, along with a formal test for normality (Shapiro-Wilk test). If the assumption of normality is violated, non-parametric tests will be applied. ANOVA with repeated measures will be used to analyse changes in quantitative data (change scores) and to compare the two groups.

Missing data will be handled using linear mixed-model analyses, which provide unbiased estimates under the assumption that data are missing at random and allow inclusion of all available observations. Furthermore, multiple imputation will be applied as a sensitivity analysis to assess the robustness of the results to potential missingness.

We will also use Bonferroni corrected post hoc comparisons when performing multiple comparisons, ensuring that the overall significance level remains accurate. Additionally, effect sizes are estimated based on Cohen’s *d* (0.2 = small effect, 0.5 = medium effect, and 0.8 = large effect).

Participants with mild-to-moderate depressive symptoms will be eligible for inclusion, as anxiety and depression frequently co-occur in clinical populations. Due to our limited sample size, formal subgroup analyses based on depression status will not be conducted. Instead, the baseline depressive symptom scores (HADS-D) will be entered as a covariate in the statistical models to adjust for their potential influence on anxiety outcomes.

Age will be included as a covariate in all primary and secondary analyses. In addition, exploratory subgroup analyses will be performed by age group (< 40 years vs ≥ 40 years).

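### The rule for serious incidents withdraws the participant from the whole study and does not separate stopping training from ending outcome collection, so willing participants' outcomes may be lost without need

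*Protocol article*

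**What the plan says.** The rule stands in the protocol article under 'Participant adherence to the intervention, adverse events and concomitant care'. After a serious incident, it says, "the participant will immediately be withdrawn from the study"; medical assessment and care follow. It covers every serious incident, whether or not training caused it, and withdrawal is from the study. The same section states that "the likelihood of any serious adverse medical event is regarded as minimal" and gives no rate.

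Three other parts bear on it:

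- 'Sample size calculation': "Sensitivity analyses based on both intention-to-treat and per-protocol datasets will be applied to assess the robustness of the findings".
- 'Statistical analysis': "Missing data will be handled using linear mixed-model analyses, which provide unbiased estimates under the assumption that data are missing at random". It adds that "multiple imputation will be applied as a sensitivity analysis to assess the robustness of the results to potential missingness". The covariates named there are age and baseline HADS-D.
- 'Methods/design' and Table 1: BAI, HADS, blood pressure and EKG are taken at baseline, t1 (straight after the last session), t2 (four weeks later) and t3 (three months after the intervention). No assessment falls between baseline and t1.

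Nothing in the article says that t1 to t3 assessments continue for a participant withdrawn after an incident.

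**The concern.** Stopping an intervention and stopping data collection are different acts. An intention-to-treat comparison needs the outcomes of everyone randomised, including those who stop training. Here the trial team would itself end observation because of something that happened after randomisation, in a person who may be willing to go on filling in questionnaires.

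The arms differ by design in exertion: 85–95% against about 60% of maximal heart rate. Incidents could therefore be unevenly spread. The BAI counts a racing heart and dizziness among its symptoms, so a physical incident could also be related to later scores. If both hold, the participants left in one arm no longer represent those randomised to it, and the primary comparison shifts. Outcomes that were never collected cannot be recovered by modelling afterwards.

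**Working it through.** **1. What is left for a participant withdrawn before t1.** Only the baseline score. There is no change score for the repeated-measures ANOVA. The mixed model keeps the baseline value at most, and in effect predicts the missing outcomes from same-arm participants who continued, given the covariates. The multiple imputation described states no departure from missing at random, so as described it does not test that assumption. For an incident between t1 and t2, the t1 score is kept. The t2 score, which 'Methods/design' labels the primary endpoint, is lost.

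**2. The plan's own figures.** Inputs from 'Sample size calculation': baseline BAI 30 in both arms; expected post scores 14 (high) and 22 (low), so a difference of 8; SD 7; two-sided alpha 0.05; power 80%; 12 per group; about 20% attrition.

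- Normal approximation: n per group = 2 × (1.960 + 0.842)² × 7² / 8² ≈ 12.02. This is 13 when rounded up, against the stated 12. Power at 12 per group is 79.9% by this approximation and 76.3% by the exact noncentral t.
- Attrition: 24 / 0.8 = 30, as stated.

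The stated figures reproduce closely enough for this purpose. A few incident withdrawals fit inside the attrition allowance, so the issue is possible bias and not sample size.

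**3. Size of a possible shift.** Let k be the number withdrawn before t1 out of 15 in one arm. Let D be the gap between their unseen mean BAI and the value the model predicts for them. Then

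shift in the BAI difference = (k / 15) × D.

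The protocol gives neither k nor D; both are assumed. D = 16 is the extreme in which a high-intensity participant stays at 30 instead of reaching 14.

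| k of 15 | D = 4 | D = 8 | D = 16 |
|---|---|---|---|
| 1 | 0.27 (3% of 8) | 0.53 (7%) | 1.07 (13%) |
| 2 | 0.53 (7%) | 1.07 (13%) | 2.13 (27%) |

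The standard error of the difference at 15 per arm is 7 × √(2/15) = 2.56. One loss therefore moves the estimate by 0.27/2.56 = 0.1 to 1.07/2.56 = 0.4 standard errors.

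**4. When the shift is zero.** It is zero if D = 0, that is, if missing at random holds given arm and observed data. It also cancels if both arms lose the same number with the same D. If D is negative, or the loss is in the other arm, the direction reverses. If outcomes are still collected after training stops, this source of error disappears.

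**5. How often the rule might be used.** With an assumed risk of 1% per participant, the chance of at least one case among 30 is 1 − 0.99³⁰ = 26%. With 2% it is 1 − 0.98³⁰ = 45%.

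**The case against.** The case on the other side is substantial.

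- **Loss of outcomes is a reading of the rule.** The article nowhere says in terms that assessments cease, and a fuller protocol is available on request. This stands in part. But the article does not merely stay silent about follow-up: it states a rule, and the rule's plain meaning ends participation. If the full protocol already keeps these visits, only the wording needs aligning.
- **A reader might infer that the losses are treatment-related.** The text does not support that. The rule covers any serious incident, and no arm-specific rate is given.
- **A reader might infer that every use of the rule biases the result and flatters the high-intensity arm.** That is too strong. Withdrawal after a recorded incident is not automatically missing not at random. Someone withdrawn late in training may already have improved, so even the direction is assumed.
- **A reader might infer that harm follow-up is cut off.** The same sentence keeps medical evaluation and treatment, and serious events go to the ethics committee. What ends, as written, is study assessment.
- **Events should be very rare.** Participants are screened by a doctor with EKG and blood tests, and severe cardiovascular and lung disease are excluded. The most likely number of cases may well be zero. This stands, and it limits the expected impact. It does not repair the rule for the case in which it is used.
- **Missing data are already addressed.** There is an attrition allowance, a mixed model and multiple imputation. None of these, as described, replaces outcomes that could have been observed.

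**Conclusion.** The point holds in a limited form. As written, the rule merges stopping training with leaving the study. This sits badly with the intention-to-treat dataset and puts avoidable weight on missing at random. Bias is possible, not established: it needs incidents that differ by arm and that relate to later anxiety beyond what the model contains. For one loss of 15 in an arm, the illustrative shift is about 0.3 to 1.1 BAI points, or 3% to 13% of the planned 8. The upper end assumes no improvement at all, and the number of events is an assumption. The likely impact is small because such events are expected to be very rare, but with 15 per arm a single case is not negligible. The change is worth making because it is cheap and the loss it prevents cannot be undone later.

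**What to change.** Leave the decision to stop training and the medical care in the adverse-events section as they are. Add that:

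- stopping training is separate from withdrawal from follow-up;
- the remaining t1 to t3 assessments are still offered unless consent is withdrawn or the participant is medically unable to attend;
- the participant is analysed in the randomised arm;
- the reason for stopping and its date are recorded.

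The cost is a sentence or two and a small amendment, for which 'Ethics and dissemination' already gives the route. The visits are already scheduled, and the primary outcomes are questionnaires. The downside is a few assessment visits by participants who no longer train.

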### Statistical analysis

Data management and analyses are performed using SPSS 30 (SPSS Inc., Chicago, IL, USA). Data will be analysed using descriptive and inferential statistics. Continuous variables are presented with mean ± SD and 95% CIs.

The effect of the intervention will be assessed by examining change scores on the BAI and HADS (primary outcomes) and blood pressure and EKG (secondary outcomes). Changes from baseline to post-tests (immediately, after four weeks, and after three months) will be analysed.

Single measures (e.g. baseline data) will be analysed using ANOVA or linear regression, provided the statistical assumptions for linear models are met. Variables will be assessed for normality through visual inspection of histograms and Q-Q plots, along with a formal test for normality (Shapiro-Wilk test). If the assumption of normality is violated, non-parametric tests will be applied. ANOVA with repeated measures will be used to analyse changes in quantitative data (change scores) and to compare the two groups.

Missing data will be handled using linear mixed-model analyses, which provide unbiased estimates under the assumption that data are missing at random and allow inclusion of all available observations. Furthermore, multiple imputation will be applied as a sensitivity analysis to assess the robustness of the results to potential missingness.

We will also use Bonferroni corrected post hoc comparisons when performing multiple comparisons, ensuring that the overall significance level remains accurate. Additionally, effect sizes are estimated based on Cohen’s *d* (0.2 = small effect, 0.5 = medium effect, and 0.8 = large effect).

Participants with mild-to-moderate depressive symptoms will be eligible for inclusion, as anxiety and depression frequently co-occur in clinical populations. Due to our limited sample size, formal subgroup analyses based on depression status will not be conducted. Instead, the baseline depressive symptom scores (HADS-D) will be entered as a covariate in the statistical models to adjust for their potential influence on anxiety outcomes.

Age will be included as a covariate in all primary and secondary analyses. In addition, exploratory subgroup analyses will be performed by age group (< 40 years vs ≥ 40 years).

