**Methods:**

Thirty adults aged 18 to 70 years diagnosed with an anxiety disorder will be recruited for this study. Participants will be randomised into an intervention group (high-intensity training) and a control group (low-intensity training). Randomisation will be performed using counterbalanced block randomisation in a 1:1 ratio, stratified by sex. Both groups will perform 4 weeks of twice-weekly training supervised by an exercise physiologist. The primary outcome will be the total score on the Hospital Anxiety and Depression Scale (HADS) and the total score on the Beck Anxiety Inventory (BAI). The secondary outcomes include blood-pressure changes and adherence. Evaluations will be performed at baseline and following 4 weeks of the interventions, and 6 months after the termination of the intervention period (secondary endpoint).

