## Methods/design

This is a study protocol for a randomised controlled trial designed to test the effects of high intensity training compared to low intensity training on anxiety levels.

There will be a random 1:1 allocation into two groups. The two groups are high intensity exercise (1 × 4 minutes performed two times per week with a heart rate of 85–95% of maximal heart rate, corresponding to ≥ 16 on the 6–20 Borg scale) and low intensity exercise (45 minutes performed two times per week with a heart rate of approximately 60% of maximal heart rate, corresponding to 9–11 on the 6–20 Borg scale) [26]. The high intensity group will perform a 10-minute warm-up prior to the high-intensity bout, and a 5-minute cooldown. Due to the low intensity in the low intensity group, a warm-up is not considered necessary.

The total amount of training sessions for both groups will be eight. The high intensity exercise group will serve as the intervention group, while the low intensity exercise group will serve as an active control group.

The trial will be conducted in accordance with the Standard Protocol Items: Recommendations for Interventional Trials statement (SPIRIT) [27].

The trial has been approved by the Data Protection Officer at the University Hospital of North Norway and the Regional Committee on Health Research Ethics (approval number 714458) and registered at ClinicalTrials.gov (Trial registration number NCT06881758).

Participants will provide written informed consent before allocation to the two intervention groups, and they will be randomised into a high-intensity training group and a low-intensity training group, following baseline measures.

Randomisation will be performed using counterbalanced block randomisation in a 1:1 ratio, stratified by sex, to ensure an equal distribution of males and females across the study groups. Block sizes of four–six participants will be used. This will allow for a balanced representation of both genders in each condition. Randomisation will be conducted using a computer-generated random number sequence via the website https://www.randomizer.org/.

Outcomes will be measured immediately after inclusion (baseline), right after the very last exercise session, four weeks after the last exercise session (primary endpoint) and three months after the termination of the intervention period (secondary endpoint) (Fig. 1).

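### BAI and HADS are both primary with no rule for success, while the sample size gives the whole two-sided 0.05 to BAI alone

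*Protocol article*

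**What the plan says.** The Abstract (Methods) gives the primary outcome as "the total score on the Hospital Anxiety and Depression Scale (HADS) and the total score on the Beck Anxiety Inventory (BAI". The Background, the Primary outcome measures section and the Statistical analysis section also treat both scales as primary; the last refers to "change scores on the BAI and HADS (primary outcomes) and blood pressure and EKG (secondary outcomes". None of them says whether a positive trial needs BAI, HADS, either or both. The first hypothesis under Hypotheses/aims and benefits speaks of anxiety levels without naming a scale.

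The Sample size calculation rests on one scale: "We assumed a baseline mean of 30 on the Beck Anxiety Inventory (BAI) for each group". It continues: "The expected post-treatment BAI scores are 14 for the high-intensity group and 22 for the low-intensity group", and then: "With a significance level (alpha) of 0.05, SD of 7 and 80% power, the required sample size is 24". It gives no expected effect or SD for HADS.

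On multiplicity, the Statistical analysis section has one sentence: "We will also use Bonferroni corrected post hoc comparisons when performing multiple comparisons, ensuring that the overall significance level remains accurate".

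Two related details also bear on the rule. The Abstract makes the HADS total primary, while the Primary outcome measures section calculates the total and both subscores. Methods/design labels four weeks after the last session as the primary endpoint, while the Primary outcome measures section takes the measurement after the last session.

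**The concern.** With two primary scales, the error rate and the power of the trial are defined only once the success rule is stated. The protocol makes two positive claims, an accurate overall level and 80% power at 0.05, without a rule under which both can be checked. The Bonferroni sentence does not settle this. If it leaves the two primaries alone, nothing protects a claim made on whichever scale is significant. If it covers them, BAI is tested at 0.025 and the sample size was calculated at the wrong level.

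The practical risk is a split result. In a trial this small, one scale could well be significant and the other not, and the protocol gives no way to call that outcome. The choice would then be made after the data are seen.

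**Working it through.** **Inputs from the protocol.** Post-treatment BAI 14 and 22, so the difference is 8; SD 7; d = 8/7 = 1.14; two-sided 0.05; 80% power; 1:1 allocation; 24 evaluable (12 per arm); 20% attrition; 30 enrolled.

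**Inputs not in the protocol (assumed).** BAI–HADS correlation ρ, mainly 0.5 to 0.8; HADS standardised effect equal to BAI (1.14), or 0.8. All figures use the plan's own unadjusted two-sample t-test at one visit.

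**1. The plan's figure.** Normal approximation: n per arm = 2 × [SD × (z₀.₉₇₅ + z₀.₈₀) / difference]² = 2 × [7 × (1.960 + 0.842) / 8]² = 12.02, which rounds to 12 per arm, or 24. Attrition: 24 / 0.8 = 30. Both stated figures reproduce. Power at 12 per arm is Φ(1.143 × √6 − 1.960) = Φ(2.799 − 1.960) = 79.9%. The exact (noncentral) t gives 76.3%, so the plan's 80% is the normal approximation.

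**2. Either scale at 0.05, uncorrected.** Type I error = 1 − P(|Z₁| < 1.960 and |Z₂| < 1.960).

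| ρ | Type I error |
|---|---|
| 0 | 1 − 0.95² = 9.75% |
| 0.5 | 9.1% |
| 0.8 | 7.8% |
| 0.9 | 7.0% |

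A simulation of t-tests at 12 per arm gives 9.2% at ρ = 0.5 and 8.0% at ρ = 0.8.

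**3. Bonferroni over the two scales (0.025 each).** The critical value becomes 2.241.

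| BAI power, 12 per arm | at 0.05 | at 0.025 | loss |
|---|---|---|---|
| Normal approximation | 79.9% | Φ(2.799 − 2.241) = 71.2% | 8.7 points |
| Exact t | 76.3% | 65.4% | 10.9 points |

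To restore 80% by the normal approximation, n = 2 × [7 × (2.241 + 0.842) / 8]² = 14.55, so 15 per arm, 30 evaluable, and 30 / 0.8 = 37.5, or 38 enrolled. By exact t, n = 15.88, so 16 per arm, 32 evaluable, and 32 / 0.8 = 40 enrolled.

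**4. Both scales required at 0.05.** There is no inflation of the error rate. The chance that both are significant at 12 per arm is:

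| HADS d | ρ | Normal approximation | Exact t (simulated) |
|---|---|---|---|
| 1.14 | 0.5 | 68.6% | 63.4% |
| 1.14 | 0.8 | 72.8% | 68.0% |
| 0.8 | 0.5 | 45.6% | 41.5% |
| 0.8 | 0.8 | 49.0% | 45.2% |

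**5. How often the scales split.** By the same simulation, exactly one scale is significant in about 26% (ρ = 0.5) to 16% (ρ = 0.8) of trials if HADS has the same effect, and in about 40% to 33% if HADS d = 0.8.

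**The case against.** **Both may be meant.** The protocol joins the two scales with *and* throughout, which can be read as requiring both. On that reading 0.05 per scale is correct, and the stated 80% remains what it was calculated to be, power for BAI; the plan claims no joint power. This stands. A reader might infer that either the error rate or the power must be wrong, and the documents do not show that. They show that the rule is unstated and that neither claim can be confirmed without it.

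**Three visits.** A reader might also count two scales at three post-baseline visits as six separate tests and derive a much larger error rate, or a much lower power after correction. The documents do not support this. The Statistical analysis section specifies repeated-measures ANOVA, and Methods/design and Primary outcome measures each name one primary time, although they disagree on which. An error rate over visits would also need a between-visit correlation that is not given.

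**Size of the power loss.** Setting 65% against the stated 80% mixes an exact t with a normal approximation. Like for like, the loss from Bonferroni is about 9 to 11 points; the rest comes from the approximation. With all 30 evaluable, power at 0.025 would be 81% (exact t 77%), but the plan itself expects 20% loss. If success meant at least one scale after Bonferroni, and HADS had the same effect, the chance of a win at 24 evaluable would be about 77–92% by the normal approximation (ρ from 0.9 to 0). The plan states neither that rule nor a HADS effect.

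**Detail left to an analysis plan.** The exact multiplicity procedure may be in an analysis plan that is not shown. That does not answer the point about sample size: the number of primaries and the level used for sizing are fixed in this document, and splitting alpha later cannot give BAI 80% power at 24 evaluable.

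**Conclusion.** The concern holds in this form: two primary outcomes, no success rule, and a sample size that covers only one of them at the full 0.05. What follows depends on the rule eventually adopted: type I error of about 8–9% (either, uncorrected), BAI power lower by about 9 to 11 points (Bonferroni), or a sound error rate with exact-t joint power of about 63–68% at best and 41–45% if HADS responds less. The BAI power figures rest only on the protocol's own inputs. The error rates and joint powers also rest on an assumed BAI–HADS correlation, and the joint powers on an assumed HADS effect. The direction is the same at every correlation tried. The rule should be settled before outcome data are analysed by group.

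**What to change.** State a fixed sequence in the protocol:

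1. Test BAI first, at one named primary visit, at two-sided 0.05. Methods/design and Primary outcome measures must be reconciled on which visit that is.
2. Test HADS at the same visit at two-sided 0.05 only if BAI is significant.
3. Report all other scales and visits with 95% confidence intervals and no confirmatory claim.

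Name the HADS score. If the anxiety subscore replaces the total given in the Abstract, say so explicitly and give the reason: 7 of the 14 items in the total concern depression, while the hypothesis concerns anxiety.

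This controls the error rate over the two scales at 5%, keeps the only sized outcome at its planned level, and adds no participants. BAI power stays at 79.9% (exact t 76.3%). The cost is that HADS no longer stands as an equal primary and cannot be claimed if BAI fails. The Trial status section has recruitment starting in January 2025, so the change needs a dated amendment made after recruitment began, and a registry update. Requiring both scales, or splitting alpha, would also be valid, but each means re-sizing the trial; the split alone needs 38 to 40 enrolled.

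### Repeated-measures ANOVA and a linear mixed model are both named without saying which decides the primary comparison, and no primary analysis set is stated

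*Protocol article*

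**What the plan says.** In the protocol article, the Statistical analysis section assigns the comparison of the arms to one method: "ANOVA with repeated measures will be used to analyse changes in quantitative data (change scores) and to compare the two groups". The next paragraph brings in a second: "Missing data will be handled using linear mixed-model analyses, which provide unbiased estimates under the assumption that data are missing at random", and adds that this model uses every observation that exists. It then says that "multiple imputation will be applied as a sensitivity analysis to assess the robustness of the results to potential missingness". Change is to be analysed at three post-tests, with Bonferroni-corrected post hoc comparisons, and no visit is singled out.

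The Sample size calculation section repeats the commitment to mixed models for missing data. Its only mention of analysis sets is this: "Sensitivity analyses based on both intention-to-treat and per-protocol datasets will be applied to assess the robustness of the findings".

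The same section powers the trial on a single time point. "The expected post-treatment BAI scores are 14 for the high-intensity group and 22 for the low-intensity group", and "This means we need 12 participants per group to detect significant differences using a two-tailed" *t*-test.

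The primary time point is given in two ways. Methods/design puts it four weeks beyond the final session, and Primary outcome measures puts it at the end of the last session.

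**The concern.** A mixed model does not repair an ANOVA. It is a separate analysis with its own group estimate and p-value. Classical repeated-measures ANOVA excludes a participant with any missing visit; a mixed model does not. When data are missing, the two can rest on different participants and give different answers, and the text does not say which one counts.

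The target can differ as well. Run over three post-baseline change scores, the ANOVA group effect is an average over visits, and its group-by-time term asks whether the effect changes between visits. Neither is the single-visit BAI difference on which the sample size rests.

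Intention-to-treat is listed only as a sensitivity dataset, so the reader cannot tell what the main result is meant to be robust against. With about 20% attrition expected, the choice of model and set could be made after the results are seen.

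**Working it through.** **1. The plan's own figure.** Inputs from the Sample size calculation section: post-treatment BAI 14 and 22 (difference 8), SD 7, two-sided alpha 0.05, power 80%.

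- n per arm = 2 × (z₀.₉₇₅ + z₀.₈₀)² × SD² / difference² = 2 × (1.960 + 0.842)² × 49 / 64 = 12.02. Rounded to the nearest whole number this is 12 per arm, 24 in total, as stated.
- With 20% attrition, 24 / 0.80 = 30, as stated.
- Power with 12 per arm is 79.9% by the normal approximation and 76.3% by the exact *t*-test (which needs 13.05 per arm).

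The stated sample size is therefore reproduced, and it belongs to a comparison at one time point.

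**2. What the literal ANOVA keeps.** If 20% is the total loss, 30 × 0.80 = 24 participants are complete, which is the planned evaluable number. If visits are instead missed independently, complete cases per arm = 15 × (1 − m)³, where m is the proportion missing at each of the three post-tests. The values of m are assumptions.

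| m (assumed) | Complete per arm | Exact-*t* power for 8 points, n rounded |
|---|---|---|
| 5% | 15 × 0.857 = 12.9 | 80% (13 per arm) |
| 10% | 15 × 0.729 = 10.9 | 72% (11 per arm) |
| 20% | 15 × 0.512 = 7.7 | 57% (8 per arm) |

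**3. What the averaged effect tests.** Assumptions: SD 7 at each visit, equal correlation ρ between visits, 12 complete per arm. The SD of a three-visit mean is 7 × √((1 + 2ρ)/3), which is 5.72 at ρ = 0.5 and 6.26 at ρ = 0.7. Exact-*t* power:

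| Difference at the three post-tests (assumed) | Average | ρ = 0.5 | ρ = 0.7 |
|---|---|---|---|
| 8 / 8 / 8 | 8 | 91% | 85% |
| 8 / 6 / 4 | 6 | 69% | 61% |
| 8 / 4 / 0 | 4 | 37% | 32% |

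Averaging helps if the difference persists and hurts if it wanes. The point is that this is a different quantity from the one powered, not that it is always weaker. The waning patterns place the full 8 points at the first post-test; if the primary visit is the second, the single-visit difference is smaller in those rows too.

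**4. Analysis sets.** The document names two datasets, both as sensitivity analyses. Nothing in it is labelled primary.

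**The case against.** The strongest reply is that the text, read as a whole, leans towards the mixed model. Two sections commit to it for missing data, one of them saying outright that it uses all existing observations. A reader might infer from the ANOVA sentence that the trial's comparison is complete-case. The documents do not settle on that; it is one of two readings. This part of the reply stands.

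A reader might also infer that no comparison at a single visit is planned. That goes too far. Change at each post-test is to be analysed, with corrected comparisons. In a two-level pre/post ANOVA, moreover, the group-by-time term is exactly the between-group difference in change at that visit. What remains is that no such contrast is named as primary, and that the two sections giving the primary time point disagree.

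On size, the completer counts under per-visit loss rest on assumed rates. At 10% per visit, 27% would be incomplete, more than the attrition the plan expects. It is also tempting to argue that dropout will follow intolerance of high intensity; the Background section instead cites higher compliance with high intensity, so the direction is unknown. Nor does bias from data missing not at random separate the two methods. If the 20% missing in one arm were truly 8 points worse than predicted, that arm's mean would be off by 0.20 × 8 = 1.6 points, but the mixed model would be affected as well.

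Finally, the plan does not claim that multiple imputation tests the missing-at-random assumption, so its use is not an error. Details of that kind may sit in an analysis plan that is not shown. The unranked methods and the labelling of intention-to-treat, however, are in the text that is shown.

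**Conclusion.** The point holds in a limited form. The article assigns the group comparison to repeated-measures ANOVA, names a mixed model separately, and does not rank them. It states no primary analysis set and no primary contrast at one visit. The literal ANOVA reading would drop participants with any missing visit and average over visits; the mixed-model sentences point the other way.

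The practical size cannot be fixed from the documents. If total loss is 20% and the difference persists, the literal reading costs little. With 10% loss per visit, or a waning difference, it costs materially. These figures depend on the assumed missingness, SD, correlation and time course. The stated sample size is not in dispute. The text should be corrected before the data are analysed.

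**What to change.** - Remove repeated-measures ANOVA as the group comparison.
- Name one primary analysis: a linear mixed model on all randomised participants as allocated, with visit as a factor and a group-by-visit term.
- Report the group contrast with its 95% CI at one declared primary visit. First reconcile Methods/design with Primary outcome measures on which visit that is.
- State that intention-to-treat is the primary set and per-protocol is supportive.
- Optionally, add a delta-adjusted multiple imputation covering both arms. It should supplement the planned imputation, not replace it. Standard multiple imputation shares the mixed model's missing-at-random assumption, so it cannot show what happens if that assumption fails.

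The cost is a few sentences and a little extra analysis. The 24 evaluable and 30 randomised participants stay as planned, and trial conduct does not change.
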